### Hypotheses

We hypothesize that implementation of RISTRA-AF will reduce initial hospitalization for ED adults (≥ 18 years) with isolated AF and atrial flutter (Aim 1).We hypothesize that implementation of RISTRA-AF will increase the proportion of ED adult health plan members eligible for anticoagulation initiation on discharge to home who are prescribed anticoagulation at the time of discharge or within the following 30 days (Aim 2).

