**Fig. 3 Fig3:**
[figure not shown]
The rate control screen in RISTRA-AF for patients with a “good heart”. A good heart is defined as one with an ejection fraction greater than 50% (based on recent echocardiography or physician gestalt) and no clinical evidence of decompensated heart failure. BB, beta-blocker; bpm, beats per minute; CAD, coronary artery disease; CCB, calcium channel blocker; dilt, diltiazem; ED, emergency department; EF, ejection fraction; eGFR, estimated glomerular filtration rate; HBS, hospital-based specialist in internal medicine; HF, heart failure; IV, intravenous; KP, Kaiser Permanente; outpt, outpatient; Pharm, pharmacologic cardioversion; pt, patient; RVR, rapid ventricular response; w/, with

Rate reduction in patients with hypotension, known left ventricular ejection fraction ≤ 50%, or decompensated heart failure is more challenging and warrants a different set of recommendations (Additional file 8). If the physician is intent on attempting electrical cardioversion in the ED and the stable patient is tolerating rapid ventricular response, we recommend against rate-reducing medications, as some evidence suggests they may reduce the effectiveness of electrical cardioversion (Additional file 9) [79]. This does not apply to patients who are to receive oral flecainide or propafenone, as they require a rate-reducing agent to block the atrioventricular node at least 30 min prior to cardioversion [28].

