#### Outcomes

The primary outcome for aim 1 is hospitalization among those with isolated AF or atrial flutter [26, 27]. This includes admission to the inpatient setting and to outpatient observation units. We selected this broad definition to distinguish hospitalization from discharge to home directly from the ED. We will undertake a sensitivity analysis using a stricter definition of hospitalization, which includes only admission to the inpatient setting, to accommodate inter-facility variation in outpatient observation practices. We will also undertake a sensitivity analysis evaluating hospitalization in the larger cohort of patients who were coded as having primary AF or atrial flutter, whether the atrial arrhythmia was isolated or not. This will allow evaluation of possible biases in coding practices and assignment of isolated status.

Secondary outcomes for aim 1 include (a) discharge to home < 24 h of ED registration; (b) total length of stay in the ED and hospital; and (c) ED administration of a long-acting rate-reducing medication among patients who received any rate-reducing medication, oral or intravenous, short- or long-acting. Long-acting rate-reducing medications include oral diltiazem XR, metoprolol tartrate, metoprolol succinate, and atenolol and intravenous magnesium sulfate, 2 g or more. We will undertake a sensitivity analysis in which only 4 g or more of intravenous magnesium sulfate will count as a long-acting rate-reducing medication, as recommended in RISTRA-AF. We are not including amiodarone among our rate-reducing medications because amiodarone can also be used for cardioversion, and we cannot readily distinguish the two indications. Another secondary outcome for aim 1 is administration of continuous IV infusion of diltiazem or esmolol, which may be reduced in patients receiving early long-acting rate-reducing medications.

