The primary outcome for aim 2 is anticoagulation initiation in eligible patients with AF or atrial flutter at the time of ED discharge to home or within the following 30 days. Eligibility includes an elevated CHA_2_DS_2_-VASc score (≥ 2 in men and ≥ 3 in women) in health plan members not currently taking anticoagulants who are being discharged to home directly from the ED. Current anticoagulation use is defined using EHR data. A patient is considered to be taking oral anticoagulation if (a) any oral anticoagulation prescription was filled in 45 days prior to the index encounter, (b) the supply of a filled prescription would include the index encounter date, or (c) active use of an oral anticoagulant was documented in the medication review during the index encounter or during the 30 days prior. A secondary outcome of aim 2 is electronic consultation of the Anticoagulant Management Service, independent of anticoagulation initiation in eligible patients (defined above).

We will measure use of RISTRA-AF but have not made it a major outcome. Use of the tool may not correlate strongly with use of the management principles that the decision support tool recommends [124]. For example, a physician may use RISTRA-AF to learn that the most effective means of electrically cardioverting an obese patient involves starting with maximal joules combined with manual pressure augmentation. This management principle is easily remembered and may be employed in future cases without recourse to RISTRA-AF. Frequency of tool use would serve as a poor indicator of frequency of optimal electrical cardioversion technique. We observed a similar pattern in prior decision support research on site-of-care decision-making for ED patients with acute pulmonary embolism. Over the course of the 4 years following the initial implementation of the decision support tool, the frequency of safe outpatient management of ED patients with low-risk pulmonary embolism increased though tool use decreased [54]. These two cases (electrical cardioversion of AF and outpatient management of low-risk pulmonary embolism) illustrate why use of our RISTRA tools is optional. We provide these tools to aid clinicians with management decisions if they feel assistance is needed. Use of the CDSS is not mandatory.

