We estimate that our stepped-wedge design (with nine clusters and 10 steps) will include approximately 3420 adult ED encounters with primary and 972 (30%) with isolated AF or atrial flutter during the 10-month roll-out period. Based on pilot data, we expect at least 567 patients in the usual care condition and 460 patients in the intervention condition with isolated AF or atrial flutter during the 10-month roll-out period. Using preliminary data at the pilot sites and the trial sites, baseline initial hospitalization rate was 26.6%. We estimate a minimally detectable 8% absolute difference in initial hospitalization rate (Aim 1) at a level of 90% power and a 2-sided test at the 2.5% significance level.

We estimated the minimum number of clusters needed to achieve 90% power based on pilot data using the National Institute of Health Stepped-wedge Group Randomized Trial Calculator [126]. We present our most conservative estimates here. For the hospitalization outcome, we assume an average of 11 eligible encounters per cluster, intraclass correlation of 0.01, the cluster autocorrelation of 0.47, and the individual autocorrelation of 0.9 with a discrete-time decay, a churn rate of 0.942 and adjustment for one cluster-level variable (annual ED census) with R [2] of 0.07. We would need only three clusters to see a decrease of 8% in hospitalization rates at 90% power, so we believe that we have adequate power in this analysis, given data from nine clusters over the course of the trial.

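### Aim 2 counts only patients sent home from the ED, a disposition Aim 1 aims to change, and no stated analysis addresses the resulting composition bias

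*Protocol article*

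**What the plan says.** In the Protocol article, Outcomes, the Aim 2 primary outcome is anticoagulation initiation at ED discharge or within the next 30 days. Eligibility requires an elevated CHA2DS2-VASc score "in health plan members not currently taking anticoagulants who are being discharged to home directly from the ED". The Objectives and the Aim 2 sample-size paragraph use the same discharged-home population.

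The Aim 1 statement under Hypotheses reads: "We hypothesize that implementation of RISTRA-AF will reduce initial hospitalization for ED adults" with isolated AF or flutter. Outcomes counts both inpatient and observation admission as hospitalisation and explains: "We selected this broad definition to distinguish hospitalization from discharge to home directly from the ED". Being sent home from the ED is thus the complement of the Aim 1 outcome and also an entry condition for Aim 2.

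The sensitivity analyses named in Outcomes all belong to Aim 1: an inpatient-only definition, all primary AF/flutter instead of isolated cases, and a higher magnesium threshold. For Aim 2, Data collection and management justifies only the restriction to health plan members. Analytics and sample size calls all analyses intent-to-treat.

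**The concern.** Membership of the Aim 2 denominator is settled after exposure. If RISTRA-AF lowers hospitalisation, intervention-period discharges will include patients who under usual care would have been admitted and so left out. If those patients start anticoagulants more or less often than other discharged patients, the Aim 2 proportion moves with no change in anyone's prescribing. Assigning patients by the condition of their cluster, as intent-to-treat requires, does not prevent this, because the imbalance arises in who is counted.

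At stake is the reading of one of the two primary outcomes. A success on Aim 1 would add an unmeasured component to the Aim 2 estimate, and the article gives no result that would reveal it.

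**Working it through.** **The yardstick.** Analytics and sample size states that nine clusters can detect a 4.9-point change in anticoagulant prescription with 80% power. This cannot be strictly reproduced, because the article gives neither the baseline prescription rate nor the significance level for Aim 2. An approximate stepped-wedge calculation used the stated inputs (seven encounters per cluster, taken as per cluster-period; intraclass correlation 0.006; cluster autocorrelation 0.356), assumed baselines of 5% to 80% and two-sided levels of 2.5% or 5%. Power was about 9% to 56% over ten periods, and 6% to 37% over 22 periods with two transition months removed. With inputs missing and the cited calculator unavailable, this is no ground for calling 4.9 wrong. It is used below only as the article's own scale.

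**Inputs from the article.**
- Isolated AF/flutter: "baseline initial hospitalization rate was 26.6" per cent, so 73.4% go home.
- Aim 1 effect: "We estimate a minimally detectable 8% absolute difference in initial hospitalization rate (Aim 1) at a level of 90% power". Hospitalisation falls to 18.6% and 81.4% go home.
- Isolated share of primary encounters: 972/3420 = 28.4% by arithmetic, 30% as stated. Both are used.

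**Assumptions, not in the article.**
- *d*: the difference in initiation between newly discharged patients and those discharged under either condition; 10, 20 or 30 points.
- *h*: hospitalisation among non-isolated primary cases; 26.6% to 80%.
- Nobody who would go home under usual care is admitted because of the intervention.
- The shift among Aim 2-eligible patients equals that among all primary cases.

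**Formula.** Let D0 and D1 be the discharged-home proportions under control and intervention. The newly discharged share is w = (D1 − D0)/D1. With no effect on prescribing, the Aim 2 proportion changes by w × d.

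**Isolated cases alone.** w = (81.4 − 73.4)/81.4 = 8.0/81.4 = 9.8%.

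**Aim 2 population (all primary AF/flutter), only isolated cases shifting.** With s the isolated share, D1 − D0 = s × 0.08 and D1 = s × 0.814 + (1 − s)(1 − h).

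| s | h | D0 | D1 | w | d = 10 | d = 20 | d = 30 |
|---|---|---|---|---|---|---|---|
| 28.4% | 26.6% | 73.4% | 75.7% | 3.0% | 0.30 | 0.60 | 0.90 |
| 30% | 50% | 57.0% | 59.4% | 4.0% | 0.40 | 0.81 | 1.21 |
| 30% | 70% | 43.0% | 45.4% | 5.3% | 0.53 | 1.06 | 1.59 |
| 30% | 80% | 36.0% | 38.4% | 6.2% | 0.62 | 1.25 | 1.87 |

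The last three columns are bias in percentage points, with the sign of d. The range is about 0.3 to 1.9 points, or 6% to 38% of 4.9.

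**What would reach 4.9 points by composition alone.** d = 4.9/0.098, about 50 points, if the isolated-case shift applied to everyone. With the diluted shift, at least 4.9/0.0625, about 78 points.

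**The case against.** The restriction has a clinical reason. The Stroke prevention section directs its actions at patients who are going home, so the discharged-home group is where the tool acts and is the group named in the Objectives. Newly discharged patients must also meet the same score, membership and no-anticoagulant conditions, which limits how far they can differ. The planned Aim 1 analysis in all primary AF/flutter will show how far disposition moved in Aim 2's parent population, so a reader could bound the problem. All of this stands, and it limits the size. It does not make the two sets of discharged patients comparable, and knowing how far disposition moved does not reveal how the added patients differ.

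Three stronger readings are tempting, and the article supports none of them.

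- *A bias near 3 points.* Multiplying 9.8% by an assumed 30 points gives 2.9. That applies the shift in isolated cases to all of Aim 2, which covers primary AF/flutter, and the 30 points have no source in the article.
- *The primary denominator must be replaced.* That would change the question in the Objectives and unsettle a sample size built on the discharged-home subgroup. It would also come late: site emails carried anticoagulation metrics from June 2022, and the protocol version is dated February 2023. Changing a primary outcome after such data have circulated has its own credibility cost.
- *The long-acting rate-reducer outcome has the same flaw.* Its denominator is patients given any rate reducer, and below Fig. 3 the article says "we recommend against rate-reducing medications". That advice covers only a stable patient tolerating the rate whose physician intends electrical cardioversion, and it excepts oral flecainide or propafenone. The Discussion says the trial did not seek more cardioversion and less rate control. The outcome is secondary, and nothing in the article gives the size of any fall in its denominator.

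**Conclusion.** The point holds as a structural weakness of modest size. The Aim 2 primary comparison is conditioned on a disposition the intervention is meant to change, and the article states no analysis that addresses it. A separate statistical analysis plan, if one exists, was not available. Under the stated assumptions the bias is about 0.3 to 1.9 points in either direction, so it could distort the Aim 2 estimate but would not by itself produce a 4.9-point difference. The figure depends on d and h, neither of which the article gives, on an Aim 1 effect of 8 points, and on the shift being confined to isolated cases. With no Aim 1 effect on disposition this component vanishes. A reader might infer that success on Aim 1 makes Aim 2 uninterpretable; the arithmetic does not support that.

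**What to change.** Keep the discharged-home primary outcome and add one prespecified sensitivity analysis for Aim 2:

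- **Population:** all health plan members with primary AF/flutter, an elevated CHA2DS2-VASc score and no current anticoagulant at ED arrival, whatever their disposition.
- **Outcome:** anticoagulant prescription at ED or hospital discharge, or within 30 days of the index visit.
- **Reporting:** beside the primary result, with a statement that the primary result will be interpreted with caution if the two disagree.

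The cost is one more query of the health record. Study setting describes that record as covering inpatient, outpatient, emergency and pharmacy data, and the score and 30-day initiation are already obtained for members. The drawback is dilution: patients whose anticoagulation is decided by inpatient teams enter the comparison, so the estimated effect may be smaller and answers a somewhat broader question. That is acceptable in a supporting analysis, and it is one reason to leave the primary outcome in place.

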#### Pilot study

We undertook an eight-month pilot study at three geographically-affiliated KP Northern California medical centers, two where the principal investigator worked and a third nearby medical center with whom emergency physicians were sometimes shared. We launched the pilot by providing a series of educational resources to the emergency physicians and adult hospitalists identical to what we used for study launch (see below). We asked the pilot study physicians to use RISTRA-AF and send us questions and comments about the user interface and the educational and guidance content. We received much helpful input and used the feedback to improve the content and presentation of RISTRA-AF as well as the accompanying educational materials (e.g., our introductory presentation). Major changes made to RISTRA-AF during the pilot phase included the following examples: We expanded our criteria of excluded co-diagnoses to include pneumonia, acute myocarditis, and acute pericarditis; we clarified the timing of post-ED follow-up as within 7 days; we reworded the hover text explaining the indications and instructions for an electronic consult to the Anticoagulation Management Service; we added a hyperlink to facilitate placement of the electronic consult; we created a “training mode” for physicians to explore RISTRA-AF on any current ED patient (regardless of RISTRA eligibility) to gain familiarity with the tool without patient enrollment; we changed formatting and wording in several places to improve clarity; we expanded the references.

Additionally, we undertook manual chart review of randomly selected cases to validate our computerized algorithm for case ascertainment (see above on eligibility criteria). Among 100 cases identified as study eligible, 98 were confirmed to be eligible. Among 50 cases with AF who were identified as having exclusion criteria, the algorithm was correct in 49 cases.

#### Educational outreach prior to launching RISTRA-AF at each study site for the pragmatic clinical trial

Our introductory educational program for physicians included three elements, undertaken in a serial fashion: (1) The first was a roughly 30-min teaching presentation given to physicians during a regularly scheduled department-wide meeting. Introductory slides were sent to the department to be available for non-attendees and were accessible via a link underneath the RISTRA-AF entry button on the landing page (Additional file 2). The presentation included instructions on how to access RISTRA-AF, the nature of its content, and the rationale and evidence base for its principal recommendations (Table 1). (2) The second educational resource was access to RISTRA-AF using “training mode,” an option available on the first screen of the application (Additional file 4). Training mode allows physicians to test drive the application on any current ED patient, whether or not the patient is eligible for the tool. This allows the physician to become familiar with the content, recommendations, hover texts, and links without formally registering the patient in the study. (3) After completing the initial training and testing the application, physicians could take a short quiz (called a training survey) to test their knowledge of RISTRA-AF content. If they failed to pass with a score of 85% or higher, we sent them “hints” (i.e., the questions with the answers highlighted) and asked them to retake the quiz. Those who passed received up to three small gift cards, one for each of their first three completed enrollments (completed = reaching the summary screen). A similar incentive model had been used in prior RISTRA studies [16].

We also included the local cardiology and adult hospitalist departments in our launch-related education. We sent a one-page executive summary to the local chiefs of both departments, along with the introductory slide deck, which they sent to their respective physicians to inform them of the application and our clinical trial. We offered to give to their departments a presentation if they wished; some invited us to explain our study at their department meeting. We also informed the ED’s local nurses and inpatient pharmacists of the study. The inpatient pharmacists worked with us to be sure each study ED had the long-acting rate-reducing medications in their ED’s automated medication dispensing system for ready access.

#### Facility-specific monthly engagement by site leads

Local site leads provide their EDs with monthly emails. The content varied month by month, but routinely included commendation to recent local RISTRA-AF users, highlights of overall study progress, and “test your knowledge” questions to keep the AF and atrial flutter education going that began in the training survey. Six months following launch at a study site, site leads presented at an ED meeting a brief overview of the application and fielded questions from their peers. Starting at month 12 (June 2022; Fig. 1), metrics were incorporated into the monthly emails that included three intra-facility comparisons: use of long-acting rate reduction medications, anticoagulation prescribing at time of ED discharge to home, and anticoagulation prescribing in the 30 days following discharge. Each graphic included metrics of the three leading EDs as well as the ED in question (see Additional file 20 for an example).

#### Data collection and management

The majority of data in the O’CAFÉ trial were extracted from the EHR, based on structured fields populated by operational processes. Likewise, most data in RISTRA-AF were auto-populated from the EHR, based on prescribed data lists or range limits. Data entry, on the other hand, occurred by physicians only during RISTRA-AF use and only for select variables (see “Physician Input” above). These data, e.g., duration of symptoms, were used in the trial only for descriptive purposes.

Missing data were rare. Aim 1, for example, addresses hospitalization and administration of long-acting rate-reducing medications, ED process of care measures available on all study patients, independent of health plan membership. Aim 2, however, requires a complete medical profile to calculate a CHA_2_DS_2_-VASc score and 30-day follow-up to identify anticoagulation initiation. For these reasons, aim 2 was limited to study patients with health plan membership. In cases where missing data pertain, we either excluded patients with missing data from the specific analysis, used multiple imputation to estimate a value for the individuals with missing data, or created indicator variables for missing values in models to determine if missingness was predictive of outcomes.

Protected health information was stored in password-protected encrypted electronic files on protected servers. Only aggregate, deidentified data will be shared outside the research team. All personal identifiers will be destroyed at the end of the study. Only the study’s analyst and research scientist ([name] and [name], respectively) will have access to the final trial dataset.

#### Analytics and sample size

The aim of the O’CAFÉ trial was to determine whether the intervention reduces hospitalization among eligible ED patients with isolated AF or atrial flutter. We also aimed to determine if the intervention was associated with increased initiation of oral anticoagulants among eligible patients at high stroke risk. To this end, we designed the trial as a superiority trial to determine if intervention sites had better outcomes than control sites.

Analysis of RISTRA-AF effectiveness will be based on comparison of intervention and control groups according to the stepped-wedge cluster randomized pragmatic trial design. All analyses for this stepped-wedge group-randomized trial will be approached using mixed model regression methods. As this is a group-randomized trial and all groups will receive the intervention, all analyses will be done as intent-to-treat. Because the CDSS is available to all ED physicians at each study site and training is given at the site level as part of the intervention initiation, all patients at a given facility will be seen by a physician with access to and knowledge of the CDSS and therefore meet the study definition of “treated.” We will not depend upon CDSS utilization data to identify patients who received CDSS-enhanced care, because as physicians became more familiar with the CDSS content and internalized it, they would be less likely to use the tool during a patient encounter but still deliver care in accordance with the CDSS recommendations. Outcome and predictor measures were derived from the EHR, based on operational processes. We will examine within- and between-cluster correlation over time to elucidate possible correlation structures, including possible time decay in the correlation over time. While intraclass correlation and the number of repeated individuals in our cohort are expected to be low based on pilot study data, we will describe the intraclass correlation and churn rates over time and by cluster. We will use descriptive statistics to examine outcome trends over time overall, by cluster and by intervention status. Following the methods for open cohort stepped-wedge designs with binary outcomes outlined by Li et. al [125], we will use mixed models to allow for clustering with appropriate correlation structures, adjusting for time effects, RISTRA-AF status, and possibly hospital-level fixed effects.

We estimate that our stepped-wedge design (with nine clusters and 10 steps) will include approximately 3420 adult ED encounters with primary and 972 (30%) with isolated AF or atrial flutter during the 10-month roll-out period. Based on pilot data, we expect at least 567 patients in the usual care condition and 460 patients in the intervention condition with isolated AF or atrial flutter during the 10-month roll-out period. Using preliminary data at the pilot sites and the trial sites, baseline initial hospitalization rate was 26.6%. We estimate a minimally detectable 8% absolute difference in initial hospitalization rate (Aim 1) at a level of 90% power and a 2-sided test at the 2.5% significance level.

We estimated the minimum number of clusters needed to achieve 90% power based on pilot data using the National Institute of Health Stepped-wedge Group Randomized Trial Calculator [126]. We present our most conservative estimates here. For the hospitalization outcome, we assume an average of 11 eligible encounters per cluster, intraclass correlation of 0.01, the cluster autocorrelation of 0.47, and the individual autocorrelation of 0.9 with a discrete-time decay, a churn rate of 0.942 and adjustment for one cluster-level variable (annual ED census) with R [2] of 0.07. We would need only three clusters to see a decrease of 8% in hospitalization rates at 90% power, so we believe that we have adequate power in this analysis, given data from nine clusters over the course of the trial.

Given that only 18% of ED encounters are eligible for stroke prevention action (discharged to home, current KP member, not currently or recently taking oral anticoagulants, and at high risk for stroke), the overall numbers of eligible encounters for the stroke prevention-related outcomes are much smaller. For the primary Aim 2 outcome (any prescription ordered for oral anticoagulation medications within 30 days of the index visit), power is still adequate in this study design to identify changes in rates of prescriptions ordered as small as 5% in the eligible subgroup. Based on pilot data and assuming an average of seven eligible encounters per cluster, intraclass correlation of 0.006, the cluster autocorrelation of 0.356, and the individual autocorrelation coefficient of zero with a discrete-time decay, and a churn rate of 0.984 with no adjustments for cluster-level variables, our nine-cluster design will allow us to identify a 4.9% change in rates of anticoagulant prescription with 80% power.

We anticipate wide variation in practice patterns across our EDs, as we have seen in the management of other conditions [54, 127, 128]. Some EDs might start the trial further from their optimal performance level than others. These EDs may have more potential for practice improvement than others and more to gain from the intervention. To account for this, we will also report facility-specific changes from pre- to post-intervention, anticipating a larger impact at facilities whose pre-intervention practices were in the lower tertile.

Given the many variables we are collecting during this trial, we also will be able to address other important clinical questions. For example: What is the association of short-acting oral rate-reduction medications (e.g., diltiazem 30 mg) with hospitalization? Is timing of administration of long-acting rate-reducing medications (e.g., early vs late in the ED course) associated with ED length of stay and hospitalization? How does hospitalization prevalence compare between those receiving different doses of intravenous magnesium sulfate? What are the prevalence and effects of administering both non-dihydropyridine calcium channel blockers and beta-blockers? Was the trial intervention associated with a change in cardioversion prevalence and success and in selection of cardioversion agents (e.g., electrical vs pharmacologic; procainamide vs ibutilide) for AF and atrial flutter? What is the association of stroke prevention actions in the ED with the short- and long-term incidence of ischemic stroke and death among patients eligible for anticoagulation on ED discharge to home? Was the trial intervention associated with other measures of patient care recommended by RISTRA-AF, e.g., ordering of thyroid-stimulating hormone and echocardiography testing when indicated?

